## Abstract

**Background:**

Spinal cord stimulation (SCS) is one of the neuromodulation therapies for chronic neuropathic pain. The conventional paresthesia-based SCS involves the application of tonic stimulation that induces a sense of paresthesia. Recently, new SCS stimulation patterns without paresthesia have been developed. Differential target multiplexed (DTM) stimulation and fast-acting subperception therapy (FAST) stimulation are the latest paresthesia-free SCS patterns.

**Methods:**

A single-center, open-label, crossover, randomized clinical trial to investigate the superiority of SCS using the latest new stimulation patterns over conventional tonic stimulation for neuropathic pain is planned. This study consists of two steps: SCS trial (first step) and SCS system implantation (second step). In the SCS trial, participants will be randomly assigned to 4 groups receiving stimulation, including tonic, DTM, and FAST. Each stimulation will then be performed for 2 days, and a visual analog scale (VAS) for pain will be evaluated before and after each stimulation pattern. A stimulation-off period for 1 day is set between each stimulation pattern to wash out the residual previous stimulation effects. Pain improvement is defined as more than 33% reduction in the pain VAS. The primary analysis will compare pain improvement between the new stimulation patterns and the conventional tonic stimulation pattern in the SCS trial. The secondary outcomes will be evaluated as follows: (1) the relationships between causative disease and improvement rate by each stimulation pattern; (2) comparison of pain improvement between the DTM and FAST stimulation patterns in all cases and by causative disease; (3) changes in assessment items preoperatively to 24 months after the implantation; (4) preoperative factors associated with long-term effects defined as continuing for more than 12 months; and (5) adverse events related to this study 3 months after the implantation.

**Discussion:**

This study aims to clarify the effectiveness of the latest new stimulation patterns compared to the conventional tonic stimulation. In addition, which stimulation pattern is most effective for which kind of causative disease will be clarified.

**Trial registration:**

Japan Registry of Clinical Trials (jRCT) 1,042,220,094. Registered on 21 November 2022, and last modified on 6 January 2023. jRCT is an approved member of the Primary Registry Network of WHO ICTRP.

## Background

Neuropathic pain is caused by lesions in somatosensory pathways of the peripheral or central nervous system. The estimated prevalence of neuropathic pain ranges from 1 to 7% [1]. Pharmacological treatment of neuropathic pain consists mainly of the use of pregabalin, antidepressants, and opioids [2]. However, many patients do not respond to pharmacological treatment. For this reason, non-pharmacological approaches such as neuromodulation therapies have been developed [3]. Spinal cord stimulation (SCS) is one of the neuromodulation therapies that has been used for decades to treat chronic neuropathic pain [4–7]. The conventional SCS consists of the application of tonic stimulation that induces a sense of paresthesia. It is essential for the amelioration of pain that the elicited paresthesia overlaps the painful area [8]. The pain relief mechanism of SCS using conventional tonic stimulation is based on the gate control theory [9, 10]. According to the theory, SCS induces activation of spinal GABAergic interneurons in the dorsal horn and descending pain-inhibitory pathways [9, 10].

Since the 2010s, several new SCS stimulation patterns without paresthesia have been developed [11–14]. These new stimulation patterns are described as “paresthesia-free” or “subperception” SCS. Differential target multiplexed (DTM) stimulation (Medtronic Inc., Minneapolis, MN, USA) and fast-acting subperception therapy (FAST) (Boston Scientific, Marlborough, MA, USA) stimulation are among the latest paresthesia-free SCS patterns, which have been available in Japan since 2021. It has been suggested that SCS with the latest stimulation patterns has higher pain relief effects than the conventional tonic stimulation [15–17]. Furthermore, the latest new stimulation patterns may be effective in cases where the conventional tonic stimulation cannot be continued because of the discomfort of the paresthesia [18–20]. Meanwhile, which stimulation is most effective for which kind of neuropathic pain remains unclear.

Whereas all SCS devices can provide conventional tonic stimulation, the new stimulation patterns are device-dependent, with each manufacturer providing its own stimulation pattern. This means that only one of the new stimulation patterns can be applied to a patient after SCS system implantation. For this study, a method that makes it possible to apply both DTM and FAST stimulation patterns to one patient during the SCS trial is performed: the Medtronic percutaneous leads are inserted and external state which applies DTM stimulation, and a Boston Scientific cable is connected to the external leads to apply FAST stimulation.

The first clinical question is whether SCS using the latest stimulation patterns for neuropathic pain provides more pain relief than the conventional tonic stimulation. The second clinical question is which kind of stimulation provides the greatest pain relief effect for which kind of neuropathic pain. The hypothesis to be tested in this study is that SCS with the latest stimulation patterns provides significantly more pain relief than the conventional tonic stimulation for patients with neuropathic pain.

## Methods/design

### Study design

This is a single-center, open-label, crossover, randomized, superiority clinical trial.

### Patient population

Patients will be selected based on inclusion and exclusion criteria as shown below. The main criterion for enrollment is intractable neuropathic pain without a history of spinal surgery at the site where the SCS lead will pass or be placed. Patients will be recruited from new patients treated according to standard clinical practice at Nagoya University Hospital.

### Inclusion criteria

Intractable neuropathic pain resistant to drug treatment using more than one drug.Age ≥ 18 years.Pain visual analog scale (VAS) score > 40.Written, informed consent.

### Exclusion criteria

Anti-cancer therapy.History of drug abuse.Histories of spine or spinal cord surgery at the site through which the spinal cord stimulation lead passes or will be placed.Local and general anesthesia cannot be performed.Conditions resulting in high surgical risk, such as unstable angina pectoris and end-stage liver disease presenting with hepatic encephalopathy.Poorly controlled diabetes mellitus (HbA1c ≥ 9%).Serious concomitant diseases (liver disease, kidney disease, heart disease, lung disease, blood disease, brain disease, etc.)Pregnant or potentially pregnant.Considered inappropriate by the head of research or researcher allocating patients.

### Who will take informed consent?

Potential participants will be identified from among patients visiting Nagoya University Hospital. After clinical research physicians assess potential participants for the inclusion and exclusion criteria, they will be given study information in detail of the purpose, procedure, potential risks, and benefits of the trial. Eligible patients will need to sign two informed consents, one held by the researcher and the other by the patient, if they wish to participate. The right of a participant to refuse to participate in this trial without giving reasons for the decision will be respected.

### Additional consent provisions for collection and use of participant data and biological specimens

The consent form received from the patients includes their agreement to use the data in related future studies. Of course, patients can only agree to the current study and not accept future studies.

### Study procedures

This trial consists of two steps. The first step is an SCS trial, and the second step is SCS system implantation. In the SCS trial, two cylinder-type leads (Model 977A190; Medtronic Inc.) will be inserted under local anesthesia and connected to an external stimulation device, and intraoperative stimulation will be performed to confirm the area of paresthesia induction. The leads will be placed at vertebral levels of the paresthesia covering the painful area and then directly sutured to the skin at the puncture sites without a skin incision. During the SCS trial, three stimulation patterns, tonic, DTM, and FAST, will be applied. After the SCS trial ends, the inserted leads will be removed in all cases. If pain relief effects are obtained in the SCS trial, the cases will proceed to the second step. More than 1 month after the SCS trial, new cylinder-type leads and an implantable pulse generator (IPG) will be implanted under general anesthesia referring to the previous X-ray of the SCS trial lead placement. The type of implanted devices will be determined as follows: leads (Model 977A190; Medtronic Inc.) and IPG (Intellis; Medtronic Inc.) will be implanted if the DTM stimulation pattern is effective; leads (Linear ST lead; Boston Scientific) and IPG (WaveWriter Alpha 32; Boston Scientific) will be implanted if FAST or tonic stimulation patterns are effective.

### Method of SCS trial

The SCS trial period will last 9 days and consist of 3 stimulation-on periods and 2 stimulation-off periods (Fig. 1). The initial stimulation will be started one day after SCS lead insertion. The pain relief effect will be assessed using a VAS scale 6 times: pre/post Stim-1, pre/post Stim-2, and pre/post Stim-3. After the assessment of post Stim-3, the SCS leads will be removed. The order of stimulations will be set differently among 4 groups. The order of stimulations is pre-determined for each group and the order of stimulations of each group is shown in Table 1. For example, the order of group 1 will be Tonic stimulation (Stim-1), DTM stimulation (Stim-2), and FAST stimulation (Stim-3). Each stimulation pattern will be performed for 2 days. There will be a 1-day stimulation-off period between each stimulation pattern (Stim-off). The participants will be randomly assigned to one of the 4 groups at the time of study registration. In other words, the order of stimulations is determined when the participants are assigned to the group.

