### Criteria for discontinuing or modifying allocated interventions

Any patients requesting to end their participation in the study can be withdrawn from the study regardless of the stage they have reached in the study process. Patients found to be pregnant or those judged ineligible to continue participating in the study by the investigators will also be withdrawn from the study.

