### Assignment of interventions: blinding

#### Who will be blinded

The randomization is single-blinded, i.e., participants do not know which group they are allocated to. Blinding of the researchers and data analysts is not possible because each stimulation pattern is not able to be completely concealed.

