#### Methods in analysis to handle protocol non-adherence and any statistical methods to handle missing data

The primary outcome will be analyzed according to a modified-intention-to-treat principle: all randomized patients who underwent SCS lead insertion will be analyzed according to their group allocation, irrespective of the treatment they received. Patients with missing outcomes will be treated as not having met the criteria for pain improvement. Missing data will not be imputed. When the case is dropped or patient’s withdrawal, the reasons will be mentioned in detail.

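### Randomisation comes before lead insertion, but the primary analysis set requires insertion, so losses in between leave the analysis after the allocation may be known

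*Protocol article*

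**What the plan says.** All statements are in the protocol article.

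- **Timing of allocation (Method of SCS trial).** "The participants will be randomly assigned to one of the 4 groups at the time of study registration". The same section adds that "the order of stimulations is determined when the participants are assigned to the group".
- **First use of the allocation (same section).** "The initial stimulation will be started one day after SCS lead insertion".
- **Knowledge of the allocation.** The section on who will be blinded states: "Blinding of the researchers and data analysts is not possible". The Concealment mechanism section says only that the web system displays the result. It does not say when or to whom.
- **Primary analysis set (section on non-adherence and missing data).** The principle is modified intention to treat: "all randomized patients who underwent SCS lead insertion will be analyzed according to their group allocation".
- **Losses after insertion (same section).** "Patients with missing outcomes will be treated as not having met the criteria for pain improvement". Reasons for dropout are to be reported in detail.
- **Where the primary result may come from (Statistical analysis).** The main model uses Stim-1 and Stim-2. If the carryover test is positive at the 10% level, Stim-1 alone is used. DTM and FAST are compared in Stim-3 only.

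**The concern.** Membership of the primary set depends on an event that follows randomisation. In the interval before that event, unblinded staff may already know the patient's order.

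The two kinds of loss are also treated differently. After insertion, a lost patient stays in the denominator as a failure, which removes any gain from losing a patient selectively. Before insertion, the patient leaves both numerator and denominator, so that safeguard is missing.

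At stake is the comparability of the groups wherever the analysis compares different patients. If losses before insertion depended on the allocated order and on prognosis, the Stim-1-only result or the Stim-3 result could be biased. Neither a larger sample nor the rule for missing outcomes would correct that.

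**Working it through.** **1. Reproduce the plan's sample size.** Inputs from the Sample size section: 80% v 50%, significance level 0.05, power 80%, 1:1. Two-sided, pooled variance, no continuity correction:

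n per arm = [1.96 × √(2 × 0.65 × 0.35) + 0.8416 × √(0.8 × 0.2 + 0.5 × 0.5)]² / 0.30² = (1.3221 + 0.5389)² / 0.09 = 38.5, rounded up to 39.

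The total is 2 × 39 = 78, as stated. Power is 81.6% with 40 v 40 and 86.7% with 46 v 46. Sample size is not the problem.

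**2. Which comparisons are exposed (Table 1).**

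| Comparison | Groups on each side | Type |
|---|---|---|
| Stim-1 and Stim-2, tonic v new | Every group has one tonic and one new pattern | Largely within patient |
| Stim-1 only, tonic v new | 1 and 3 v 2 and 4 | Between patients |
| Stim-3, DTM v FAST | 3 and 4 v 1 and 2 | Between patients |

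In the first row, losing a patient removes an observation from both sides. In the other two rows it removes an observation from one side only.

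**3. Size under an assumed extreme.** The article gives no number of losses before insertion. The only related figure is the overall allowance of 23 − 20 = 3 per group, which is 2 × 3 = 6 of 46 in each Stim-1 arm. That allowance covers losses during the whole study. Putting all of it before insertion is my assumption.

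Suppose there is no true difference, and k would-be non-responders are lost before insertion from one arm only. With response rate p, the observed rate in that arm is 46p / (46 − k). For p = 50% and k = 6, this is 23/40 = 57.5%, a shift of 7.5 percentage points.

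The chance of a significant result in an unadjusted two-sided 5% test, by normal approximation:

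| Response rate p | k | Observed rate | Shift (points) | Rejection rate |
|---|---|---|---|---|
| 50% | 0 | 50.0% | 0 | 5.0% |
| 50% | 3 | 53.5% | 3.5 | 6.2% |
| 50% | 6 | 57.5% | 7.5 | 10.6% |
| 65% | 3 | 69.5% | 4.5 | 7.3% |
| 65% | 6 | 74.8% | 9.8 | 16.2% |

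The 65% rate is the mean of the planned 80% and 50%. The table assumes perfect foresight of response and no matching loss in the other arm.

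**4. Cost of simply counting everyone.** If 6 per arm were lost before insertion regardless of order and counted as failures, the planned rates would become 0.80 × 40/46 = 69.6% and 0.50 × 40/46 = 43.5%. Power for Stim-1 alone would be 72.1%, against 81.6% in the modified set (40 v 40). For patients already randomised, an all-randomised analysis therefore serves better as a sensitivity analysis than as the primary one.

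**The case against.** The strongest reply is that the exposed interval is narrow and the incentive weak. Every group has the same insertion, the same leads and all three patterns; only the order differs. Once the leads are in, the patient stays in the set whatever follows. No loss before insertion is reported or predicted, and nothing suggests that such losses depend on order. The main crossover analysis is largely within patient. The 7.5-point shift needs response to be foreseen before any stimulation. All of this stands, and it limits the point to a cheap improvement. It does not remove the asymmetry between losses before and after insertion.

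A reader might also infer four stronger things that the article does not support:

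- **That insertion completes eligibility.** The consent section has the criteria assessed before study information is given, and insertion is not one of them.
- **That the discretionary exclusion works after allocation.** "Considered inappropriate by the head of research or researcher allocating patients" is an enrolment criterion, so it belongs to that same earlier assessment.
- **That investigators may withdraw patients at any stage.** The article says "those judged ineligible to continue participating in the study by the investigators will also be withdrawn from the study" but names no stage there. The wording about stage applies to patients who ask to leave.
- **That staff can choose lead position to suit the order.** The Study procedures section sets one rule for all groups, based on paresthesia coverage, and the same leads deliver all three patterns.

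Finally, the article does not say that the operating team sees the allocation before insertion. The full protocol may settle this, which is why the point is worded as an opportunity.

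**Conclusion.** The point holds in limited form. The primary set is conditioned on an event after randomisation, in a trial whose researchers are not blinded, and losses before that event vanish while later ones count as failures. The between-patient comparisons, Stim-1 only and Stim-3, are the ones exposed. The article shows an opportunity for selection and nothing more.

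The size cannot be estimated from the article. The 50% to 57.5% figure is an illustration under extreme assumptions: 6 of 46 lost in one arm only, all before insertion, and all correctly foreseen as non-responders. Any realistic bias would be smaller and may be zero. The change is still worth making, because the order is not needed until the day after insertion and the article gives no reason for allocating sooner.

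**What to change.** - **Method of SCS trial.** Confirm eligibility and register as now, but run the web randomisation, or release the order, only after the leads are inserted and before Stim-1. The existing one-day gap allows this. For patients randomised from then on, the modified and full intention-to-treat sets coincide. The required 78 is unchanged.
- **Patients already randomised at registration.** The Trial status section dates the first recruitment to February 2023, so the change cannot cover everyone. For these patients, keep the present modified set as primary, report losses before insertion by group, and add a sensitivity analysis of all randomised patients, with those not inserted counted as not improved.

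The cost is a protocol amendment, a changed trigger in the web system, and an allocation step that moves into the hospital stay. No visit, procedure or staff is added. If only the order is withheld and randomisation stays at registration, no one can select on it, but the two sets could still differ, so losses before insertion should still be reported by group.

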**Fig. 1 Fig1:**

The schedule of stimulation patterns and timing of pain assessments. The SCS trial period will last 9 days and consist of 3 stimulation-on periods and 2 stimulation-off periods. The initial stimulation will be started 1 day after SCS lead insertion. The pain relief effect will be assessed using a VAS scale 6 times: pre/post Stim-1, pre/post Stim-2, and pre/post Stim-3. After the assessment of post Stim-3, the SCS leads will be removed

**Table 1 Tab1:** The order of stimulations for each group

	Stim-1	Stim-2	Stim-3
Group1	Tonic	DTM	FAST
Group2	DTM	Tonic	FAST
Group3	Tonic	FAST	DTM
Group4	FAST	Tonic	DTM

*DTM* differential target multiplexed, *FAST* fast-acting subperception therapy

### Setting of each stimulation pattern

Tonic stimulation is a conventional stimulation pattern that delivers mild electrical pulses and elicits paresthesia. Stimulation parameters include frequency, pulse width, and voltage. Frequency (10–100 Hz) and pulse width (40–300 μs) will be set by clinical research physicians so that the patient feels the paresthesia as a comfortable sensation. After setting both frequency and pulse width, the voltage will be adjusted by the patient using a remote control.

DTM stimulation is one of the latest paresthesia-free stimulation patterns that delivers multiple electrical signals and stimulates multiple locations without paresthesia. DTM stimulation consists of one stimulation signal on the upper side of the leads, called the base program, and multiple stimulation signals on the lower side of the leads, called the prime program. The base program is set at a frequency of 50 Hz, pulse width of 200 μs, and voltage of approximately 70% of the paresthesia threshold. Three prime programs are set at the lower side of the base program. The prime program is set at a frequency of 300 Hz, pulse width of 170 μs, and voltage of approximately 65% of the paresthesia threshold. DTM stimulation delivers electrical signals from the base and three prime programs. Patients do not use a remote control during DTM stimulation.

FAST stimulation is a latest paresthesia-free stimulation pattern that delivers two symmetrical biphasic waveforms to the leads with a frequency of 90 Hz and a pulse width of 210 μs. Each wave is a rectangular phase of the charge-balanced stimulation cycle. During the first rectangular phase, a negative current is injected through negatively configured leads, and a positive current is injected through positively configured leads. During the second rectangular phase, the polarities are reversed to achieve charge balance. Then, positive and negative reversal stimulations are repeated. The stimulation power is lowered to approximately 30% of the paresthesia threshold. Patients do not use a remote control during FAST stimulation.

### Criteria for discontinuing or modifying allocated interventions

Any patients requesting to end their participation in the study can be withdrawn from the study regardless of the stage they have reached in the study process. Patients found to be pregnant or those judged ineligible to continue participating in the study by the investigators will also be withdrawn from the study.

### Strategies to improve adherence to interventions

All treatments will be administered to participants during their stay in the hospital by attending surgeons. Therefore, participants’ adherence to interventions is assured.

### Relevant concomitant care permitted or prohibited during the trial

All other treatments will be allowed.

